### Data Management

Participant consent forms and all data collection will be administered online via Qualtrics. Data will be stored on Qualtrics and will be accessible only to research personnel who are granted access by the research staff. Participants will receive a link to the consent form via email with instructions on how to complete the form. After signing the online consent form, each participant will schedule a video call meeting, during which they will complete baseline data collection measures with the help of the study manager. Immediately after the participant and study manager complete the baseline questionnaire, the study manager will leave the call and be replaced by the research staff, who will randomize the participant into the intervention or the control group using the secure online software [32]. The participants will be given instructions based on their group allocation and asked not to reveal their group to the study manager, who will remain masked to the randomization result. Participant IDs and group allocation will be recorded on a secure, password-protected digital tracking sheet. Only research personnel involved with the group allocation will have access to the tracking sheet, and the study manager will not be able to access any information on the sheet related to participant group allocation. At T2 and T3 timepoints, participants will be sent an email containing a unique link to the next Qualtrics questionnaire and will be asked to complete the survey on their own.

### Data Analysis

#### Statistical Analysis

All data analysis will be conducted by the research team independently from the study sponsor. Descriptive analysis will be used to describe our sample and consider clinical outcomes and study feasibility. The most current versions of R statistical software (R Foundation for Statistical Computing) [58] and IBM SPSS software [59] will be used. The 1-sample Kolmogorov-Smirnov test will be performed to evaluate data distribution. Demographic and outcome variables will be summarized by groups using means (SDs), frequencies, and proportions. Similar to previous feasibility studies [60], the means (SDs) calculated in the feasibility RCT will be used to estimate the effect size and the variance necessary for the full RCT. Focuses of the analysis will include investigating differences in primary and secondary effectiveness outcomes for the intervention and control groups at each timepoint. We will include an interaction between time and group for all models to account for the possibility of effect modification by time. Estimated marginal means will be used to conduct post hoc analyses, and pairwise comparisons of estimated marginal means will be conducted to examine specific differences between groups at each timepoint. Participant IDs will be used as a random effect. Multiple imputations will be used to deal with missing data. Furthermore, descriptive statistics will be used to assess participants’ online usage data of the eHealth program (eg, the amount of time participants spent accessing the modules) to evaluate feasibility indicators (dose level response, treatment adherence) related to resource and treatment issues [61].

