## Methods

### Study Design

This paper provides the details of a study protocol for a concurrent mixed methods study, including a feasibility randomized controlled trial (RCT). The study is registered with ClinicalTrials (NCT06364813). The purpose of the feasibility RCT is to (1) assess the fidelity of the process, resource, management, and treatment indicators and (2) estimate the parameters needed for a large-scale, multisite RCT [24]. Secondary objectives will be to assess the effect of COMPANION on primary and secondary clinical outcomes for fcSCI [24,25].

To assess the feasibility and intervention fidelity of COMPANION, a 6-month feasibility RCT with a 1:1 allocation ratio will be conducted, comparing COMPANION with the standard education and resources available to fcSCI. The study will incorporate quantitative and qualitative design methods administered through surveys and a final exit interview. In conjunction with RCTs in rehabilitation, the use of qualitative methods has been recommended to spot unexpected variables and findings [26,27]. The interview will be an opportunity for participants to share perspectives about their experience using COMPANION, with findings used to interpret clinical outcomes and, when integrated with quantitative findings, identify patterns and paradoxes between the results.

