### Sample Size and Inclusion and Exclusion Criteria

Suggested sample sizes for a feasibility RCT range from 12 to 30 per experimental group [28,29]. We aim to recruit at least 20 participants per group. Inclusion criteria for participants are, at the time of recruitment, as follows:

Family caregiver of an adult individual with SCI (similar to previous studies of this population [30,31]; in this study,family caregiveris defined as an individual who is primarily responsible for providing immediate informal daily care for a relative with SCI).Age >18 years.Living with the individual with SCI in the community.Living in North America.SCI of the patient has not happened within the previous 6 months.

Those fcSCI who had major medical and physical conditions that require routine visits to medical doctors (eg, cancer) will be excluded from the study, in addition to fcSCI providing care to individuals with SCI who are still patients in a rehabilitation facility.

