**Process**			
	Recruitment rate	Number of participants recruited, number of women and men recruited	Mean of 3-4 participants/month: total of 40
	Consent rate	Percentage of participants consenting	<10% participant refusal
	Retention rate	Percentage of participants with T3^a^ data	Complete data collection for >80%
	Perceived benefit	Responses to the SUS^b^, qualitative interviews at T3	>85% of responses strongly agree/agree, qualitative analysis informing clinical importance
	Assessor masking	Percentage unaware of group status	100% of participants not unmasking their treatment

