## Results

This research was funded by the Craig H Neilsen Foundation PSR Pilot Grant (PSR2-17) beginning in April 2022. After the first 2 study phases, during which COMPANION was codeveloped with caregiver partners, recruitment and data collection for the RCT began in June 2024 and is currently ongoing. We enrolled 54 participants at the end of baseline. Data collection was completed in April 2025. Data analysis for the RCT is expected to begin in June 2025. The fcSCI randomized into the intervention group have been given access to COMPANION after randomization.

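### The plan takes the effect size for the full RCT from the feasibility means (SDs), but the feasibility trial is too small to supply it

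*Protocol article*

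**What the plan says.** - **Use of the pilot.** Statistical Analysis states that "the means (SDs) calculated in the feasibility RCT will be used to estimate the effect size and the variance necessary for the full RCT". It cites earlier feasibility studies as precedent.
- **Status of that use.** Study Design makes it one of the two purposes of the feasibility RCT to "estimate the parameters needed for a large-scale, multisite RCT".
- **Pilot size.** Sample Size and Inclusion and Exclusion Criteria says "We aim to recruit at least 20 participants per group". The basis is a rule of thumb: "Suggested sample sizes for a feasibility RCT range from 12 to 30 per experimental group". Table 1 repeats the total: "Mean of 3-4 participants/month: total of 40".
- **Actual size.** Results reports "We enrolled 54 participants at the end of baseline", and Study Design specifies 1:1 allocation.
- **Outcome.** The primary clinical outcome is the 12-item Zarit Burden Interview, scored 0 to 48. The article gives no expected SD and no minimal important difference for it.

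Nothing else in the article limits how the pilot effect size is to be used.

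**The concern.** This is a stated choice, not a gap that an analysis plan might fill: the article names the pilot means as the source of the effect size for the definitive trial. A pilot sized by a 12 to 30 per group rule of thumb gives a workable estimate of an SD but a very imprecise estimate of a difference between groups. Required sample size varies with the inverse square of the effect, so errors in the effect are magnified in the size. If the pilot overstates the effect, the multisite trial is underpowered. If it understates it, the trial is planned far larger than needed. If the observed effect is zero or in the wrong direction, no size can be computed.

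**Working it through.** **Inputs from the article.** Planned: 20 per group, 2 × 20 = 40, which agrees with Table 1. Enrolled: 54, so 54/2 = 27 per arm if the 1:1 split is even. Retention expectation: above 80% with T3 data, and 0.8 × 27 = 21.6, taken as 21. No alpha, power, effect size or SD stands behind the pilot size, and no size is given for the full RCT, so there is no figure of the plan's own to reproduce beyond the total of 40.

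**Assumptions not in the article.** Two-sided alpha 0.05, 80% power, normal data, unadjusted two-group comparison, true standardised difference d from 0.3 to 0.8.

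**Step 1, precision of the pilot effect.** SE(d) = √(2/n + d²/(4n)). At an observed d of 0.5:
- n = 27: √(0.0741 + 0.0023) = 0.276, half-width 1.96 × 0.276 = 0.54, 95% CI −0.04 to 1.04.
- n = 21: √(0.0952 + 0.0030) = 0.313, half-width 0.61, 95% CI −0.11 to 1.11.

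**Step 2, what that does to the planned size.** Full-trial n per arm = 2(1.96 + 0.84)²/d² ≈ 15.7/d². At n = 27 the upper limit of 1.04 implies 15.7/1.08 ≈ 15 per arm. The lower limit, being negative, gives no usable size.

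**Step 3, how often the planned size is badly wrong.** Planned n is below half the need when the observed d exceeds √2 times the true d. It is more than double the need, or not computable, when the observed d is below the true d divided by √2. True power is below 50% when the observed d exceeds the true d by a factor above 2.80/1.96 = 1.43.

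Hand check at true d = 0.5 and n = 27 (normal approximation):
- Above 0.707: z = (0.707 − 0.5)/0.276 = 0.75, probability about 0.23.
- Below 0.354: z = −0.53, probability about 0.30.
- Sum: about 0.53.
- Power below 50% (observed d above 0.714): z = 0.78, probability about 0.22.

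Using the noncentral t distribution of the observed d, at 27 per arm:

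| True d | Needed per arm | Off by more than a factor of 2, or no usable size | True power below 50% |
|---|---|---|---|
| 0.3 | 175 | 70% | 32% |
| 0.4 | 99 | 61% | 27% |
| 0.5 | 63 | 53% | 23% |
| 0.8 | 25 | 33% | 13% |

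At true d = 0.5 the middle half of planned sizes runs from about 33 to 157 per arm against a need of 63. At 21 per arm the figures are somewhat worse: 65% and 30% at d = 0.4, 39% and 16% at d = 0.8.

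**Step 4, the same pilot used for the SD only.** The 95% CI for the SD is 0.84 to 1.24 times the estimate at 27 per arm. Suppose the target is fixed in scale points and happens to equal 0.5 true SD (63 per arm). Planned n is then 42 to 90 per arm (central 95%) and true power 63% to 92%. A factor-of-two miss occurs in about 0.1% of pilots, against 53% when the observed effect is used.

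**The case against.** The strongest defence is that the sentence speaks only of estimating an effect size and a variance. It gives no formula, and the Discussion says only that findings can inform the design of a definitive RCT, which will need its own sample-size justification. The harm therefore falls on a later trial: this trial's feasibility verdicts and group comparisons are untouched. That limits the severity. It does not remove the point, because the article names the pilot as the source of the effect size and offers no other.

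Two further replies carry some weight. The planned models use repeated measures, which may improve precision, but the quoted rule refers to means and SDs. The problem is also milder if the true effect is large, as the d = 0.8 row shows.

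Several stronger readings are tempting but not supported:
- A reader might infer that the pilot effect will be applied mechanically. The article does not say so.
- A reader might infer that a small pilot effect would lead to the full trial being abandoned. Under Feasibility, each objective is judged a success or in need of revision against Table 1, and no Table 1 indicator is the between-group difference in burden.
- A reader might argue that unmasked participants and self-reported outcomes inflate the pilot effect and so undersize the full trial. A full trial against usual care with the same outcomes would presumably share that bias. It bears on validity and does not show a sizing error.
- A reader might fault the lack of an upper confidence limit on the SD. The article is silent on how the SD enters the later calculation, and silence on that in a condensed article is no fault.

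**Conclusion.** The concern holds for the effect size and not for the variance. The pilot difference has a 95% half-width of about 0.54 SD at 27 per arm and 0.61 at 21. For true effects of 0.3 to 0.5 SD, sizing on it would miss by more than a factor of two, or fail, in more than half of pilots; at 0.8 SD, in about a third. These figures rest on the alpha, power, range of d and unadjusted comparison assumed above, and on an even split of the 54. The change should be made. It affects the planning of the definitive trial, not the conduct or feasibility conclusions of this one.

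**What to change.** In Statistical Analysis, remove the effect size from what the pilot supplies and state instead:
- the full RCT will be sized on a minimal important difference in the 12-item Zarit score, expressed in scale points and fixed with the caregiver partners before the pilot group difference is seen;
- the pilot supplies the SD, the baseline-to-follow-up correlation and retention;
- the pilot group difference is reported with its 95% CI as descriptive only.

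This costs one sentence and no new data. The article says that analysis has not begun, so as of its writing the difference can still be set in advance. The downside is that the important difference must be argued for, and the planned full trial may be larger than the pilot effect would have suggested.

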### Study Timeline

The following 3 data collection timepoints will be used in the feasibility RCT: the time immediately following successful screening of the participants, during which baseline data will be collected and access to COMPANION will be provided to participants in the intervention group; 3 months after baseline data collection (T2); and 6 months after baseline data collection (T3). Please see Multimedia Appendix 1 for further information about the study timeline.

As of June 2024, recruitment and data collection for the study began and are ongoing. All data collection is performed via a secure online survey tool available through our institute (Qualtrics). After successful screening, randomization, and baseline data collection have been conducted, participants will be asked to complete the baseline survey. Follow-up data will be collected at 3 months (T2) and 6 months (T3). At baseline-T3, participants will respond to measures that assess primary (subjective burden) and secondary (objective burden, relationship quality satisfaction, distress, physical and mental health, and caregiving competence) outcomes. The purpose of baseline is to collect baseline information about the outcomes of the study. The purpose of T2 is to capture the influence of the intervention on our psychological outcomes of interest (eg, depression, anxiety, stress, and competence). T3 reflects the optimal change period for self-reporting of physical outcomes (eg, physical health and functioning).

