### Randomization and Masking

Upon successful enrollment and baseline data collection, participants are randomized by the research staff using the online service Sealed Envelope [32] with a block size that is undisclosed to the study manager. The research staff is responsible for randomization and the delivery of the intervention, while the study manager, who is responsible for enrolling participants and conducting data collection, remains masked to the participants’ group allocation. To mitigate performance bias, participants are instructed not to discuss their program or group allocation with any member of the research team, except the research staff, and both the study manager and research staff will continue to reinforce this point when contacting participants. The research staff is responsible for receiving emails from participants and removing information related to group allocation before forwarding participant emails to the study manager.

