### Clinical Outcome Measures: Primary Outcome

Clinical outcomes will be measured via a digital survey administered at baseline, T2, and T3. The components of the survey and outcome measures are detailed next.

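### As worded, the between-group contrasts at T2 and T3 are in essence not adjusted for the baseline score, which costs precision and lets chance baseline imbalance move the clinical effect estimates

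*Protocol article*

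**What the plan says.** Under Statistical Analysis the protocol article gives three elements of the outcome models. The first is the interaction: "We will include an interaction between time and group for all models to account for the possibility of effect modification by time". The second is the clustering term: "Participant IDs will be used as a random effect". The third is the contrast, described as post hoc: "pairwise comparisons of estimated marginal means will be conducted to examine specific differences between groups at each timepoint".

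Study Timeline lists baseline, T2 (3 months) and T3 (6 months) as the three data collection timepoints. The primary-outcome section adds: "Clinical outcomes will be measured via a digital survey administered at baseline, T2, and T3". Each clinical outcome measured at all three visits therefore has a baseline value. Randomization and Masking places that value before allocation: "Upon successful enrollment and baseline data collection, participants are randomized by the research staff". Data Management describes the same order.

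No baseline covariate, change-from-baseline contrast or equal-baseline constraint is named. A separate sentence takes the planning inputs for the definitive trial, effect and variability, from the means and SDs observed here. The target size is stated as: "We aim to recruit at least 20 participants per group". Results reports 54 enrolled.

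**The concern.** If groups are compared at every timepoint and baseline is one of them, baseline belongs to the outcome vector. It is then not a covariate, and the group means at baseline are not constrained to be equal, since that contrast would otherwise be zero by construction. The T2 and T3 contrasts therefore make essentially no use of each participant's starting score.

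This has two consequences. Precision is given up although the data needed to gain it are already collected. In a small trial, part of any chance difference in starting burden also reappears in the T2 and T3 contrasts and may be read as an effect of COMPANION. The between-group comparison at baseline itself answers no question about the intervention: any difference there arose before treatment.

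**Working it through.** **The plan's own figure.** The sample size rests on a rule of thumb (12 to 30 per group), so there is no power calculation to reproduce. 2 × 20 = 40 agrees with the total in Table 1.

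**Inputs.** From the article: n = 20 per arm planned; 54 enrolled at 1:1, about 27 per arm; outcomes at baseline, T2 and T3. Assumed, because the article does not give it: the baseline-to-follow-up correlation r, taken as 0.5 to 0.7, with 0.4 to 0.8 as a wider range. Results are in SD units because no SD for the Zarit score is stated.

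**Step 1: does the random effect adjust for baseline?** With group, time and their interaction, the six group-by-time means are fitted freely. With complete data, the T3 contrast (group coefficient plus interaction coefficient) must then equal the difference in observed T3 means. Fitting this model to simulated data confirmed it:

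- r = 0.5: contrast −0.5179, raw difference −0.5179.
- r = 0.7: contrast −0.2149, raw difference −0.2149.

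So neither the random intercept nor the interaction adjusts this contrast.

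**Step 2: precision.** SE unadjusted = √(2/n). SE baseline-adjusted = √(2/n) × √(1 − r²).

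| n per arm | Unadjusted | Adjusted, r = 0.5 | Adjusted, r = 0.7 |
|---|---|---|---|
| 20 | √(2/20) = 0.316 | 0.316 × √0.75 = 0.274 | 0.316 × √0.51 = 0.226 |
| 27 | √(2/27) = 0.272 | 0.272 × √0.75 = 0.236 | 0.272 × √0.51 = 0.194 |

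The variance cut is r²: 25% at 0.5 and 49% at 0.7 (16% to 64% over r = 0.4 to 0.8). In sample-size terms, 1/(1 − 0.25) = 1.33 and 1/(1 − 0.49) = 1.96.

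The formula ignores the cost of estimating the slope. In 20,000 simulated trials at 20 per arm, the SDs of the estimates were 0.318 against 0.279 (r = 0.5) and 0.317 against 0.231 (r = 0.7). That is a variance cut of 1 − (0.279/0.318)² = 23% and 1 − (0.231/0.317)² = 47%.

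**Step 3: chance imbalance.** The baseline difference has SD √(2/n).

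- P(above 0.5 SD in either direction) = 2Φ(−0.5/0.316) = 11% at 20 per arm and 2Φ(−0.5/0.272) = 7% at 27.
- Above 0.3 SD: 34% and 27%.

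The unadjusted contrast moves by about r × imbalance. A 0.3 SD imbalance shifts it by 0.15 to 0.21 SD, and a 0.5 SD imbalance by 0.25 to 0.35 SD. In the simulations, the slope of the unadjusted contrast on the baseline difference was 0.505 (r = 0.5) and 0.696 (r = 0.7). For the adjusted estimate it was 0.008 and −0.002. The unadjusted estimates averaged about zero (−0.0008 and −0.0001) with no true effect, so there is no bias over repeated randomization.

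**Step 4: would the interaction coefficient serve instead?** It equals the difference in change from baseline, with SE √(2/n) × √(2(1 − r)). At 20 per arm this is 0.316 (r = 0.5) or 0.245 (r = 0.7), against 0.274 or 0.226 adjusted. It also over-corrects for imbalance: slopes −0.495 and −0.304.

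**The case against.** The strongest reply is that the article does not list every model term. It names an interaction and a random effect and excludes no covariate, and covariate lists are often left to an analysis plan. That stands as a limit: a reader might infer that the plan rules out baseline adjustment, and it does not. But the contrast it does fix, between groups at each timepoint with baseline among the timepoints, does not fit either form of adjustment. The point rests on that wording and not on silence alone.

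Other parts of the reply also stand.

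- **Post hoc label.** The contrasts are called post hoc, and the interaction in every model does carry the difference in change. The article gives the interaction a different purpose, effect modification by time, and does not name it as the effect estimate.
- **Missing data.** Estimated marginal means equal raw means only with complete data. With dropout, the model and the planned multiple imputation bring in some baseline information.
- **Bias.** A reader might infer a biased estimate. There is none on average; the error is conditional on the imbalance that happens to occur.
- **Likelihood.** A reader might infer that large imbalance is to be expected. Chances of 11% or 7% above 0.5 SD do not support that.
- **Planning inputs.** A reader might infer that these contrasts feed the definitive trial's sample size. The article takes those inputs from the descriptive means and SDs, so changing the model alone would not change them.
- **Stakes.** Clinical effects are a secondary objective, the trial has no powered hypothesis, and no Table 1 criterion uses a between-group contrast.

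**Conclusion.** The point holds in moderate form. As worded, the T2 and T3 contrasts are valid and unbiased on average, but in essence unadjusted for a baseline score that is already collected. Adjustment would cut their variance by about 25% to 49% at r = 0.5 to 0.7, slightly less after estimating the slope, and would remove nearly all their dependence on chance baseline imbalance.

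The size rests on the assumed correlation, on complete data, and on equal arms of 20 or about 27. It also rests on baseline being measured before allocation, as Randomization and Masking and Data Management both say. The Abstract and Study Timeline word the order differently and should be brought into line.

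The Table 1 decisions between success and revision do not depend on this.

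**What to change.** 1. For each outcome measured at all three visits, model T2 and T3 as the outcomes, with the baseline value of the same measure as covariate plus group, time, group × time and the participant random effect. A constrained longitudinal model with a common baseline mean is an alternative.
2. Report the adjusted group differences at T2 and T3 with 95% confidence intervals. Drop the between-group comparison at baseline and keep the descriptive baseline summary by group.
3. Amend the sentence on means and SDs so that the definitive trial's planning inputs come from this analysis: adjusted difference, residual SD and baseline-to-follow-up correlation. Step 1 alone leaves that sentence untouched. For illustration only, at an assumed effect of 0.5 SD, two-sided 5% and 80% power, 2 × (1.96 + 0.84)²/0.5² gives 63 per arm unadjusted. Multiplying by 1 − r² gives 48 (r = 0.5) or 33 (r = 0.7).

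The cost is a wording change and a few lines of R or SPSS, with no new data. The article states that analysis had not begun, so the change can be dated before any group comparison is seen.
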